## Abstract

**Background::**

With the increase in the prevalence of chronic diseases, enhancing immunity has become an important challenge. Health functional foods, such as *Phellitus linteus* (PL), are known to improve immune function. In previous laboratory studies, it has been reported that PL has anticancer activities. In this study, we will evaluate if PL improves immune functions in adults with reduced immunity and identify its effects on immunity factors.

**Methods::**

This study will be a single-center, randomized, double-blinded, and placebo-controlled trial. Study participants will be randomly allocated to 3 experimental groups: those taking PL 1000 mg, PL 2000 mg, or placebo. Total duration of the clinical trial will be 8 to 10 weeks. Study participants will have follow-up visits every 4 weeks and the effect and safety will be assessed at the second and third visits. All participants will be asked to maintain a dosage schedule for this protocol. The primary outcome will be natural killer (NK) cell activity and the secondary outcomes will include peripheral white blood cell (WBC) count; levels of tumor necrosis factor (TNF)-α, interferon (IFN)-γ, and interleukin (IL)-1β, IL-2, IL-6, and IL-12 to assess autoimmune reactivity; and levels of immunoglobulin (Ig)G1, IgG2, and Immunoglobulin M (IgM) to assess allergic activity. Repeated measure analysis will be used to measure primary efficacy based on full analysis set.

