### Outcome measures

2.6

The primary outcome is NK cell activity, which will be used to assess immune reactivity. The secondary outcomes are peripheral WBC count; levels of TNF-α, IFN-γ, IL-1β, IL-2, IL-6, and IL-12 to assess autoimmune reactivity; and levels of IgG1, IgG2, and IgM to assess allergic activity. URI symptoms will also be recorded. All outcome measures will be observed at every visit. For the safety of the participants, we will conduct laboratory tests, such as liver function panels, complete blood counts, and electrolyte levels, and we will evaluate vital signs. Safety assessments will be conducted at the second and third visits. Participants’ data will be anonymized and coded by a specific program.

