### Statistical analysis

2.8

Statistical analysis will be performed using the principle of full analysis set. For intention-to-treat (ITT) analysis, missing values will be analyzed by last observation carried forward (LOCF). The baseline values before treatment and the changes in NK cell activity at 4 weeks and after treatment will be measured for the 2 experimental groups and the control group. If the data follow a normal distribution, an independent *t* test will be performed to test the differences between 2 groups of continuous variables. If not, Mann–Whitney *U* test will be performed. Paired *t* tests will be performed to test the differences between groups if the data follow a normal distribution. If not, Wilcoxon signed-rank test will be performed. The test of normality for continuous variables will be analyzed using the Shapiro-Wilk test. The confidence level will be set at 5%. All statistical analyses will be performed using SPSS Statistics for Windows Version 20.0 (IBM Corp., Armonk, NY).

Drinking alcohol, which can affect the weekly evaluation, is considered a management variable, and if there is a difference between groups, an analysis of covariance (ANCOVA) will be performed. Descriptive statistics, such as number of subjects, mean, standard deviation, minimum, median, and maximum will be presented for baseline, at each visit, and at final evaluation. Change from baseline to final evaluation will be reported for continuous data, clinical laboratory tests, and vital signs. For categorical data, a division table will be provided. If necessary, 95% confidence intervals will be calculated. No intermediate analysis will be performed.

Demographic variables measured during the screening period will be summarized for each treatment group. Assays for comparison of drug administration groups will be performed. For this purpose, the continuous data will be tested using the *t* test or Wilcoxon rank-sum test. Categorical data will be analyzed using a chi-square test or Fisher exact test.

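### The Abstract names a repeated-measures analysis for primary efficacy, but section 2.8 contains none and does not say which of its own tests, dose contrasts or visits is primary

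*Protocol article*

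**What the plan says.** The Abstract (Methods) is the only place that ties a method to primary efficacy: "Repeated measure analysis will be used to measure primary efficacy based on full analysis set".

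Section 2.6 names the endpoint: "The primary outcome is NK cell activity, which will be used to assess immune reactivity".

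Section 2.8 describes the data for that endpoint: "The baseline values before treatment and the changes in NK cell activity at 4 weeks and after treatment will be measured", across all three arms. The tests come directly afterwards:
- The between-group comparison when normality holds: "If the data follow a normal distribution, an independent *t* test will be performed to test the differences between 2 groups of continuous variables". Non-normal data go to the Mann–Whitney test instead.
- A second family of tests, also described as comparing groups: "Paired *t* tests will be performed to test the differences between groups if the data follow a normal distribution". The signed-rank test is its fallback.
- The t/rank choice rests on a normality check: "The test of normality for continuous variables will be analyzed using the Shapiro-Wilk test".
- ANCOVA is added if the groups differ in alcohol use.

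Section 2.8 also sets a 5% level and imputes missing values by LOCF. It mentions no repeated-measures method, no deciding visit, no deciding dose contrast and no rule for two doses.

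**The concern.** A repeated-measures analysis of three arms over three visits tests a group or group-by-time pattern. A two-group t test on change tests one dose contrast at one visit. A Mann–Whitney test concerns a shift in ranks. They can give different answers on the same 30 participants.

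A reader of the Abstract and a reader of section 2.8 would therefore expect different primary results. If the text does not fix which result counts, the 5% level has no single test to attach to. The paired-test sentence adds to the confusion: parallel arms contain no natural pairs across groups, so a paired test can only compare visits within a group.

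**Working it through.** **Step 1. The two places side by side.**

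| | Abstract, Methods | Section 2.8 |
|---|---|---|
| Method | Repeated-measures analysis | Independent t or Mann–Whitney; paired t or signed-rank; conditional ANCOVA |
| Called primary? | Yes | No test is labelled primary |
| Arms per test | Not stated | Two for the t and Mann–Whitney tests |
| Visit that decides | Not stated | Not stated (week 4 and end of treatment both described) |
| Rule for two doses | Not stated | Not stated |

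The method in the first column does not appear in the second.

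**Step 2. Inputs for sizing the consequence.** From the article: three arms at 1:1:1 (section 2.1), 10 per group (section 2.3), post-baseline assessments at weeks 4 and 8 (section 2.5), 5% level (section 2.8). The total agrees: 3 × 10 = 30. The 10 per group comes from a pilot-study rule of thumb, so there is no power figure to reproduce. Assumed: two-sided tests, normal data, equal correlation between visits, no dropout.

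**Step 3. Upper guide for several unadjusted t tests, if independent.**
- Two doses at week 8: 1 − 0.95² = 9.75%.
- Two doses at two visits: 1 − 0.95⁴ = 18.5%.

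The real tests share a placebo arm and a baseline, so the true figures are a little lower.

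**Step 4. Simulation under no effect** (20,000 trials per setting, correlation 0.3 to 0.9). The repeated-measures test is the group-by-time F test with (3 − 1)(3 − 1) = 4 and 3 × 9 × 2 = 54 degrees of freedom. The t tests are on change from baseline versus placebo.

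| What may be claimed | Type I error |
|---|---|
| Repeated-measures interaction test alone | 4.8–5.0% |
| One week-8 t test | 4.8–5.2% |
| Either dose, week-8 t test | 8.8–9.4% |
| Any of four dose-by-visit t tests | 15.8–16.3% |
| Repeated-measures or either week-8 t test | 11.2–11.7% |
| Repeated-measures or any of the four t tests | 16.7–17.2% |

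The extra freedom to switch to the repeated-measures test adds about 2 points at week 8 (about 9% to 11–12%) and about 1 point with both visits (about 16% to 17%). Most of the excess over 5% is there without it.

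**Step 5. How often the verdicts differ.** The comparison is the repeated-measures test against either dose by week-8 t test. The alternative row uses correlation 0.5 and week-8 effects of 0.4 SD (low dose) and 0.8 SD (high dose), half of that at week 4.

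| Scenario | Disagreement, t tests unadjusted | Disagreement, Bonferroni for two doses |
|---|---|---|
| No effect | about 8–9% | about 5–6% |
| 0.4 / 0.8 SD | about 24% | about 16% |

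Under those effects the rejection rates are about 24–25% (repeated measures), 43–44% (either dose, unadjusted) and 32% (either dose, adjusted). The share of the disagreement due to missing dose adjustment is (24 − 16)/24, about one third.

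As a range, compare the repeated-measures test with the high-dose week-8 t test alone. For high-dose effects of 0.5 to 1.0 SD and correlation 0.5 to 0.7, they disagree in 14–26% of trials.

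**Step 6. Does naming a model suffice?** With baseline-adjusted week-8 contrasts for both doses (complete data, as an approximation to the mixed model), at least one rejects in about 9.3–9.4% of null trials if unadjusted, and in 4.5–4.9% with Bonferroni. A multiplicity rule has to accompany the model.

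**The case against.** The strongest defence is that only the Abstract assigns a method to primary efficacy. Section 2.8 never calls its t or Mann–Whitney tests primary, and they could be supporting comparisons beside a repeated-measures analysis set out in a fuller plan. This stands in part: the link between those tests and the primary outcome is inferred from their position after the NK cell activity sentence and from the absence of any other method for it. It does not remove the mismatch, because the article's full statistical section omits the method its Abstract names and ranks none of the tests it lists. An unseen analysis plan could settle the choice, but the published text would still need aligning.

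Four stronger readings are tempting, and the document does not support them.
- *Pairwise t tests discard the week-4 data.* Section 2.8 introduces the tests straight after mentioning change at 4 weeks and after treatment. Nothing limits them to week 8; that focus belongs to the simulation.
- *The Shapiro–Wilk step invalidates the 5% level.* It is a rule stated in advance, not a choice made after seeing results. In null simulations with 10 per arm, the gated procedure rejected in 4.2% (normal), 5.1% (lognormal, sigma 0.5) and 4.8% (sigma 0.8) of trials. It can send two doses or visits to different tests, which is untidy but does not break the error rate.
- *The sponsor will report whichever test is favourable.* The text leaves room for this but shows no such intent.
- *The unresolved test decides the trial.* This is a 30-person pilot with no power calculation or success rule, so that is too strong. It does name a primary outcome and a 5% level, so clarification is due.

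**Conclusion.** The inconsistency is real and stands in the current text: the Abstract names a repeated-measures analysis, while section 2.8 has none and leaves the primary test, contrast and visit open. It can change the conclusion, with disagreement in about 24% of trials at 0.4/0.8 SD, or about 16% once the t tests are adjusted for two doses. The error rate from unrestricted choice is about 11% (week 8 only) or 17% (both visits). The unadjusted doses and visits account for most of that, and the choice between methods for little.

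The null figures hardly move for correlations from 0.3 to 0.9. The disagreement under an effect depends on effect sizes and correlations that the article does not give, and all figures assume normal, complete data. The matter should be settled before unblinding.

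**What to change.** In section 2.8, name a single primary analysis:
- A mixed model for repeated measures of NK cell activity on the full analysis set, with arm, visit, arm-by-visit and baseline NK activity.
- Primary contrasts: each dose versus placebo at week 8, with 95% confidence intervals.
- A stated multiplicity rule for the two doses, for example Holm, or high dose first and then low dose.
- The scale (raw or log) fixed beforehand.
- Observed data in this model, not LOCF values.

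Then label the t and Mann–Whitney tests supportive, correct the paired tests to within-group comparisons, and word the Abstract and section 2.8 identically.

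The cost is minor rewording. Under Holm, the smaller of the two p-values must fall below 0.05/2 = 0.025. Under the ordered rule, the low dose is tested only if the high dose succeeds. The software already named has a mixed-model procedure, and no change to visits or sample size is needed.

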**Discussion::**

This study has limited inclusion and exclusion criteria and a well-controlled intervention. It will be the first randomized controlled trial to assess the efficacy and safety of PL in adults with reduced immunity. This study will provide insights into the mechanisms underlying the immune-stimulating effects of PL and lay the groundwork for further studies.

## Introduction

1

As the prevalence of chronic diseases is increasing, treatments for enhancing immunity are receiving more attention.^[1]^ Immune-related treatments can involve 2 approaches: enhancing an individual's immunity, which aims to strengthen the body's biological defense mechanisms and alleviating hypersensitivity, which aims to control allergic reactions. It is known that along with aging, immunological biomarkers deteriorates, it can increase the frequency and severity of inflammation and the incidence of self-immune diseases and cancer.^[2]^

As nutrition plays an important role in maintaining the immune functions of the human body, increasing attention has been paid to health functional foods, as they are known to have effects on improving immune function.^[3]^ One health functional food, *Phellitus linteus* (PL), belongs to the fungal family *Hymenochaetaceae* and grows on mulberry trees.^[4]^

In previous studies, the anticancer activity of PL has been examined. In 1968, Ikekawa et al^[5]^ reported that hot water extracts from *Polyporaceae* mushrooms inhibit the growth of sarcoma-180, and among those, PL extract was highly effective. Oh^[6]^ reported that proteoglycan separated from PL increases the production of interleukin (IL)-12 (IL-12) and interferon-γ (IFN-γ). Kong et al^[7]^ also reported that water extract of PL may be associated with augmentation of natural killer (NK) cell function in cancerated hosts. PL is known to suppress tumor growth, invasion, and angiogenesis^[8]^ and PL is also known to cause tumor regression by inducing apoptosis.^[9]^ Several other studies have reported that PL stimulates humoral and cell-mediated immunity by stimulating T-lymphocytes, NK cells, macrophages, and B-lymphocytes.^[10–12]^

This study protocol was designed to verify the safety and efficacy of PL on the immune system using a single-center, randomized, placebo-controlled, and double-blinded clinical pilot trial.

## Methods

2

### Study design

2.1

This study has been designed as a double-blinded, single-center, randomized clinical trial for investigating the efficacy of PL in immune functions. A total of 30 subjects with reduced immunity will be recruited from outpatients at DUCKMH through advertisements posted on bulletin boards at hospitals and apartments. Recruitment commenced in October 2019 and the trial is expected to end in December 2020. All participants will receive a full written explanation of the study's protocol and an informed consent form.

During screening, medical history within the past 6 months and drugs taken within the past 4 weeks will be recorded. Additionally, blood tests for liver function, complete blood count, and immune function will be performed.

A total of 30 adults with reduced immunity who meet the eligibility criteria for this study will be randomly assigned in a 1:1:1 ratio to treatment group 1 (PL 1000 mg), treatment group 2 (PL 2000 mg), or control group (placebo). The intervention will begin within 2 weeks of the screening visit.

Based on their study group, the subjects will be administered PL 1000 mg, PL 2000 mg, or placebo for 8 weeks. The total duration of the clinical trial will be 8 to 10 weeks. Subjects will have follow-up visits every 4 weeks, and the efficacy and the safety will be assessed at the second and third visits. The study flow chart is presented in Fig. 1.

**Figure 1 F1:**
[figure not shown]
Study design for PL clinical trial. The treatment or control groups will be administered PL 1000 mg or PL 2000 mg or placebo. The subjects will receive PL 1000 mg or PL 2000 mg or placebo for 8 weeks and will visit every 4 weeks. PL = *Phellitus linteus*.

### Inclusion and exclusion criteria

2.2

The inclusion criteria are as follows: age 20 to 65 years; peripheral white blood cell (WBC) count between 3 × 10^3^/μL and 8 × 10^3^/μL; history of upper respiratory infection (URI) symptoms twice or more within 1 year prior to the study; and written consent for participating in the trial.

The exclusion criteria are as follows: clinically significant cardiovascular, immune, respiratory, hepatobiliary, renal and urological, nervous, musculoskeletal, psychological, infectious, and/or neoplastic diseases that are currently being treated; uncontrolled hypertension or diabetes mellitus; history of vaccination within 1 month of the study; aspartate aminotransferase (AST) or alanine aminotransferase (ALT) levels over 120 IU/L; creatinine over 2.4 mg/dL (man) or 1.8 mg/dL (woman); intake of health functional foods that may affect the immune system within 2 weeks of the study; severe gastrointestinal symptoms like heartburn and indigestion; pregnancy or breastfeeding; food allergies to foods related to PL; participation in the other clinical trials during the study; intake of drugs of other clinical trial within 4 weeks of the study.

### Sample size calculation

2.3

We have demonstrated in both in vitro and in vivo experiments that PL has immunological effects. To determine the minimum effective concentration, PL was administered at various concentrations, and 200 and 400 mg/kg of PL was administered to mice for 7 days. Based on the United States Food and Drug Administration (FDA)'s guidelines for calculating the effective dose in humans, we used body surface area to translate the effective dose in animal studies to human studies. Based on these calculations, the effective dose in the human body was set at 960 and 1920 mg. For ease of production and intake, the dose was set at 1000 and 2000 mg. According to Whitehead et al^[13]^ in preliminary parallel-designed studies when effect size is considered medium, the empirically optimal sample size is 10 persons per group, due to considerations of feasibility, estimated average, and dispersion accuracy. Therefore, we designed a pilot study with 10 subjects in each group.

### Randomization and blinding procedures

2.4

Randomization will be performed by stratified block randomization method in treatment groups 1 and 2 and control group at a ratio of 1:1:1 to ensure a balanced distribution of the 3 groups. Subjects who meet all registration criteria will be randomly assigned to a randomization identification code (e.g., PLI-R-001, PLI-R-002, …, PLI-R-030) in the order generated by a computer randomization program. The randomization number will be given to each participant, and it will indicate whether PL 1000, 2000, or placebo is to be given. As this pilot study is designed to be double-blinded, the participants, researchers, and assessors collecting the data will be blinded to the group allocation. Information about intervention assignment will be stored in the third statistical department. The randomization code will be placed in an opaque envelope and stored at the hospital. With the exception of disclosure to individual patients with serious adverse events (SAE), randomization and blinding will not be disclosed to researchers until the end of the trial.

### Intervention

2.5

All eligible participants will receive treatment according to their allocated group, either PL 1000 mg, PL 2000 mg, or placebo, during the 8-week treatment period. To maintain the double-blinded nature of the study, PL 1000 mg, PL 2000 mg, and placebo will be manufactured to be similar in appearance by Hankookshinyak Pharmaceutical Co. (Nonsan, Republic of Korea) and 2 tablets will be taken orally twice a day. The subjects will be evaluated twice in 8 weeks (at 4 and 8 weeks).

### Outcome measures

2.6

The primary outcome is NK cell activity, which will be used to assess immune reactivity. The secondary outcomes are peripheral WBC count; levels of TNF-α, IFN-γ, IL-1β, IL-2, IL-6, and IL-12 to assess autoimmune reactivity; and levels of IgG1, IgG2, and IgM to assess allergic activity. URI symptoms will also be recorded. All outcome measures will be observed at every visit. For the safety of the participants, we will conduct laboratory tests, such as liver function panels, complete blood counts, and electrolyte levels, and we will evaluate vital signs. Safety assessments will be conducted at the second and third visits. Participants’ data will be anonymized and coded by a specific program.

### Data collection and monitoring

2.7

During the screening period, the subjects will fill out a questionnaire about their sociodemographic characteristics, provide a medical history from the last 6 months, provide a drug history from the past 4 weeks, and undergo laboratory tests. Personal information and data collected during the screening period will be managed by the hospital. Monitoring of data and research performance will be performed regularly by Jeneolurl Bio Taek Co., Ltd. (Pusan, South Korea). The final exam dataset will be accessible to statisticians and key investigators. The results of this study will be published in a peer-reviewed article.

### Statistical analysis

2.8

Statistical analysis will be performed using the principle of full analysis set. For intention-to-treat (ITT) analysis, missing values will be analyzed by last observation carried forward (LOCF). The baseline values before treatment and the changes in NK cell activity at 4 weeks and after treatment will be measured for the 2 experimental groups and the control group. If the data follow a normal distribution, an independent *t* test will be performed to test the differences between 2 groups of continuous variables. If not, Mann–Whitney *U* test will be performed. Paired *t* tests will be performed to test the differences between groups if the data follow a normal distribution. If not, Wilcoxon signed-rank test will be performed. The test of normality for continuous variables will be analyzed using the Shapiro-Wilk test. The confidence level will be set at 5%. All statistical analyses will be performed using SPSS Statistics for Windows Version 20.0 (IBM Corp., Armonk, NY).

Drinking alcohol, which can affect the weekly evaluation, is considered a management variable, and if there is a difference between groups, an analysis of covariance (ANCOVA) will be performed. Descriptive statistics, such as number of subjects, mean, standard deviation, minimum, median, and maximum will be presented for baseline, at each visit, and at final evaluation. Change from baseline to final evaluation will be reported for continuous data, clinical laboratory tests, and vital signs. For categorical data, a division table will be provided. If necessary, 95% confidence intervals will be calculated. No intermediate analysis will be performed.

Demographic variables measured during the screening period will be summarized for each treatment group. Assays for comparison of drug administration groups will be performed. For this purpose, the continuous data will be tested using the *t* test or Wilcoxon rank-sum test. Categorical data will be analyzed using a chi-square test or Fisher exact test.

The safety assessment will calculate the rate of adverse events. Continuous data, such as comparisons between groups, individual laboratory test results, and biomarkers will be analyzed using paired *t* tests or *t* tests with 95% confidence intervals within the group to see if there are any changes compared with the baseline. If normality is not met, nonparametric statistics (Wilcoxon signed-rank test or Wilcoxon rank-sum test) will be performed. Categorical data will suggest frequencies and ratios for each category. The difference between groups will be analyzed using chi-square test and Fisher exact test.

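### LOCF, the only stated handling of missing values, can bias the week-8 difference in NK cell activity when the effect is still building or dropout differs by arm

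*Protocol article*

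**What the plan says.** Section 2.8 (Statistical analysis) sets the analysis population with "Statistical analysis will be performed using the principle of full analysis set", without defining that set. It then states, for the ITT analysis, that "missing values will be analyzed by last observation carried forward (LOCF"). It names no other method, no assumption about why values are missing and no sensitivity analysis.

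On what is analysed, the same section says that "the changes in NK cell activity at 4 weeks and after treatment will be measured", and for the comparison that "an independent *t* test will be performed to test the differences between 2 groups of continuous variables", with the Mann–Whitney U test if normality fails. Section 2.5 places the two post-baseline evaluations at weeks 4 and 8, and section 2.6 adds that "All outcome measures will be observed at every visit".

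The Abstract describes the primary analysis differently: "Repeated measure analysis will be used to measure primary efficacy based on full analysis set". Section 2.8 does not carry this through. Section 2.9 says that people who withdraw consent are excluded from the study.

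**The concern.** With one baseline and two later visits, little can be carried forward. Someone lost after week 4 is analysed at week 8 with a half-course value. Someone lost before week 4, if kept in the analysis set, is given the baseline value and hence a change of exactly zero. Either substitution is right on average only if NK activity would not have changed further, and an 8-week course gives no reason to assume that.

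If the effect is still growing, LOCF shrinks the estimated difference. If NK activity drifts in all arms and dropout differs between arms, LOCF can produce a difference that does not exist. With 10 per arm, each dropout is 10% of an arm. A pilot's estimates are also what a later trial would be planned on, and the Discussion says that this study is meant to lay the ground for further work.

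**Working it through.** **Inputs from the protocol article.** 10 per arm, 3 × 10 = 30 in total, which agrees with the stated total (2.3, 2.1). Visits at baseline, week 4 and week 8 (2.5, 2.6). Two-sample t test on changes, 5% level (2.8), taken as two-sided because sidedness is not stated. The 10 per arm comes from a cited pilot rule without an SD, difference or power, so there is no figure to reproduce and the sample size is not disputed here.

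**Assumptions, because the protocol gives no values.** SD 1 at each visit and correlation 0.5 between visits, so the SD of a change is √(2 × (1 − 0.5)) = 1. Week-8 effect 0.80 SD and week-4 effect 0.40 SD. Dropout 10% to 30%, unrelated to the outcome.

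**1. Attenuation.** Expected LOCF difference = (share observed at week 8) × 0.80 + (share lost after week 4) × 0.40 + (share lost before week 4) × 0. With 2 of 10 lost in each arm:

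- both after week 4: 0.8 × 0.80 + 0.2 × 0.40 = 0.72 (−10%)
- one before, one after: 0.8 × 0.80 + 0.1 × 0.40 + 0.1 × 0 = 0.68 (−15%)
- both before week 4: 0.8 × 0.80 = 0.64 (−20%)

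With dropout split evenly before and after week 4, the share of the effect kept is 92.5%, 85% and 77.5% at 10%, 20% and 30% dropout. In simulation (40,000 trials) the LOCF estimates were 0.74, 0.68 and 0.62, with 95% interval coverage of 94.7%, 94.2% and 92.8%. Analysing only the observed week-8 values gave 0.80 with 95% coverage.

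**2. Unequal dropout, no true effect.** LOCF difference = −(difference in the share lost before week 4) × drift.

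- drift 1 SD, 3 PL against 0 placebo: −0.3 × 1 = −0.30 SD, simulated type I error 9.4%
- drift 0.5 SD, 2 against 0: −0.2 × 0.5 = −0.10 SD, simulated type I error 5.2%

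**3. Where there is no bias.** With no effect and equal dropout, the bias is 0 and type I error about 5%. If the effect is already 0.80 at week 4 and all dropouts leave later, LOCF returns 0.80.

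**4. Power and standard error, 2 of 10 lost per arm.**

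| Lost per arm | Power, LOCF | Power, observed week 8 only |
|---|---|---|
| 1 before, 1 after week 4 | 0.318 | 0.324 |
| 2 before week 4 | 0.302 | 0.319 |
| 2 after week 4 | 0.330 | 0.320 |

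Power with no dropout is 0.40. The fall to about 0.32 appears with or without LOCF.

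The reported LOCF SE is 0.433 against a true sampling spread of 0.426 (one before, one after), and 0.413 against 0.400 (two before). It does not understate the variability of the LOCF estimate. It is smaller than the SE from the 8 per arm measured at week 8, √(2/8) = 0.50.

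**The case against.** A reader might draw four stronger conclusions that the check or the documents do not support.

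- **That LOCF costs power.** Setting 40% beside 32% charges LOCF with the cost of having 8 rather than 10 people measured. The table above shows nearly the same power without LOCF.
- **That LOCF understates uncertainty.** Its SE matches or slightly exceeds the spread of the LOCF estimate. The gap from 0.41 to 0.50 compares two different estimators, and in these scenarios coverage is lost through bias.
- **That the bias is certain.** It depends on the time course and on dropout by arm, which the protocol does not give. The 9% type I error needs a large common drift and a lopsided, early dropout pattern. The milder case barely moves the error rate.
- **That the Abstract's repeated-measures analysis already makes LOCF unnecessary.** The Abstract does not say which kind. A classical repeated-measures analysis of variance needs complete cases, so missing values would still have to be handled.

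Two points limit the scope. Baseline is carried forward only if the full analysis set keeps participants with no post-baseline value. The exclusion of consent withdrawals in 2.9 may also leave fewer people for LOCF to reach. Finally, this is a small pilot, and sensitivity analyses may sit in an analysis plan that is not shown. That is fair as to omissions, but the point here concerns a method that 2.8 does state.

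**Conclusion.** The point holds as a conditional bias. LOCF is the only stated method, and the visit schedule leaves only a week-4 or baseline value to carry. With 2 of 10 lost per arm and an effect still building to 0.80 SD, the week-8 estimate is expected to be 0.64 to 0.72 SD. With no effect but drift and unequal early dropout, a false difference of about −0.10 to −0.30 SD arises, with type I error from about 5 to 6% up to about 9%. These sizes rest on the assumed effect, drift, linear time course and dropout; the standard errors, coverage, power and error rates also rest on the correlation of 0.5. Claims of lost power or of an SE too small for the LOCF estimate are not part of the conclusion. The plan should be changed, because a better method is available at little cost and fits what the Abstract promises.

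**What to change.** In 2.8, replace both the LOCF sentence and the primary two-sample t test/Mann–Whitney comparison of NK cell activity. Suggested text: *The primary analysis of NK cell activity is a likelihood-based mixed model for repeated measures using all observed baseline, week-4 and week-8 values, assuming that missing values are missing at random. No values are singly imputed. LOCF, if reported, is a labelled sensitivity analysis.* This also delivers the repeated-measures analysis named in the Abstract. Define the full analysis set, and reconcile the exclusion of consent withdrawals in 2.9 with the ITT analysis in 2.8.

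The cost is a few sentences in 2.8, with no change to recruitment, visits or treatment. The interval will be wider than under LOCF, up to roughly 15 to 20% at 20% dropout. Using observed week-8 values only, the SE ratios are 0.50/0.433 = 1.15 (one lost before and one after week 4) and 0.50/0.413 = 1.21 (two lost before), and the mixed model recovers part of this from the other visits. The wider interval reflects the data actually observed. The model still relies on the missing-at-random assumption.
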